## Abstract

**Introduction::**

Psoriasis is a common, recurrent, immune skin disease, which seriously affects patients’ quality of life. In clinical practice, modified Runji ointment can effectively treat mild-to-moderate psoriasis with blood dryness syndrome, but there is a lack of high-quality evidence-based medical evidence. This trial aims to evaluate the efficacy and safety of nano-modified Runji ointment in the treatment of mild-to-moderate psoriasis with blood dryness syndrome.

**Methods/design::**

This study will be a randomized double-blind placebo-controlled trial. A total of 80 patients will be recruited and randomly divided into an intervention group (nano-modified Runji ointment group) and a placebo group at a ratio of 1:1. All included patients will receive 8 weeks of nano-modified Runji ointment or placebo ointment respectively, twice a day. The primary outcome will be the change in psoriasis area and disease severity index score at week 8 compared to baseline. The secondary outcomes will be rash area score, pruritus score, Dermatology Life Quality Index score, traditional Chinese medicine symptom score and adverse events.

**Discussion::**

This study may provide high-quality evidence for the efficacy of nano-modified Runji ointment in the treatment of mild to moderate psoriasis with blood dryness syndrome. The results of this study will be published in peer-reviewed journals.

**Trial registration::**

ChiCTR, ChiCTR2000034292. Registered July 1, 2020, https://www.chictr.org.cn/edit.aspx?pid=55884&htm=4

## Introduction

1

Psoriasis is a common chronic inflammatory skin disease.^[1]^ Epidemiology surveys worldwide have found that its incidence is about 2%.[^2^,^3^] Most scholars believe that psoriasis is an inflammatory response caused by an abnormal immune system,[^4^,^5^] accompanied by a variety of skin rashes.^[6]^ Psoriasis vulgaris is the most common type of psoriasis.^[7]^ The pathological feature of psoriasis vulgaris is continuous inflammation, leading to uncontrolled proliferation and dysfunctional differentiation of keratinocytes.[^8^,^9^] Common symptoms of psoriasis vulgaris include itching, burning, and pain.^[10]^ The severity of rash was reversible. Most patients with psoriasis vulgaris exhibit recurrence characteristics. Within a few weeks or months, the number and area of rashes increase rapidly.^[11]^

For patients with mild to moderate psoriasis, most of the current diagnosis and treatment guidelines recommend the use of topical medicine.[^12^,^13^] Topically applied medicines can be absorbed through the skin into local blood microcirculation and directly act on skin lesions. At the same time, the first-pass effect of the liver and gastrointestinal inactivation of oral administration can be avoided. The constant blood concentration or physiological effects of the skin lesion can be maintained, and the action time can be prolonged. The most common topically applied medicines are glucocorticoids, tretinoin, vitamin D3 derivatives, and other drugs. Topically applied medicines have relatively satisfactory clinical effects. However, long-term use of glucocorticoid drugs can cause skin atrophy, telangiectasia, hirsutism, etc^[14]^; use of tretinoin drugs can cause irritant dermatitis, photosensitivity, etc[^15^,^16^]; some patients use vitamin D derivatives with side effects such as skin irritation and burning sensation.^[13]^

In clinical practice, external treatment with traditional Chinese medicine (TCM) also has a positive effect. Runji ointment is a common medicine used to treat psoriasis with blood dryness syndrome by ancient TCM doc. Our pre-experiment showed that modified Runji ointment can alleviate the symptoms of dry skin rash and itching in patients with psoriasis of blood dryness syndrome, and promote the regression of the rash.^[17]^ However, the particle diameter of TCM preparations is relatively large, which affects the transdermal absorption rate of the medicine. In recent years, some scholars have proposed nano-drug delivery systems (NDDS),[^18^,^19^] that is, by NDDS,^[20]^ the particle radius of the drug is smaller, and the surface area is larger. The drug's adhesiveness is improved, thereby improving the bioavailability of the drug; and nano-drugs can pass through some physical barriers and have a wider distribution range, which enhances drug utilization.^[21]^ The objective of this study was to evaluate the efficacy and safety of nano-modified Runji ointment compared with placebo ointment in the treatment of mild to moderate psoriasis with blood dryness syndrome.

## Registration and ethics

2

Before the first patient was enrolled in this study, it was registered with the Chinese Clinical Trial Registry, registration no. ChiCTR2000034292 (2020/07/01. http://www.chictr.org.cn/edit.aspx?pid=55884&htm=4). This study was conducted in accordance with the principles of the Declaration of Helsinki (2014 edition). The protocol was reviewed and approved by the Medical Ethics Committee of Shunyi Hospital of Beijing Traditional Chinese Medicine Hospital (approval number 2020SYKY01–02, protocol version number: 2nd version, version date: April 19, 2020).

## Patient recruitment and informed consent

3

This study will be a multicenter randomized double-blind placebo-controlled trial, including an 8-week treatment period and a 16-week follow-up period. The study design will follow the CONSORT Extension for Chinese Herbal Medicine Formulas 2017: Recommendations, Explanation, and Elaboration^[22]^ for reporting. A total of 80 participants will be recruited from the Dermatology Clinics of Shunyi Hospital of Traditional Chinese Medicine and Beijing Hospital of Traditional Chinese Medicine. Before enrollment, the principal investigators of each center will introduce the potential benefits and risks of the study to the participants. All participants will sign an informed consent form before being enrolled in the study.

## Inclusion criteria

4

The inclusion criteria were as follows: meeting the diagnostic criteria for Western medicine psoriasis vulgaris; meeting the syndrome differentiation standard for psoriasis with blood dryness syndrome; aged 18 to 65 years; mild or moderate degree of skin lesions (skin area < 30% of body surface area); and signed the informed consent form. The informed consent process was in accordance with the provisions of good clinical practice.

## Exclusion criteria

5

Any of the following cases will be excluded: patients treated with vitamin D 3, retinoic acid, or corticosteroids within 1 month; those who are allergic to the study drug; complicated with cardiovascular, cerebrovascular, liver, kidney, hematopoietic system, and other serious primary diseases and mental patients; pregnant or lactating women with family planning within 3 months; and patients who are participating in clinical trials with other drugs.

## Randomization

6

The random sequence will be generated by the professionals of the data management center using SAS 9.2 software (SAS Institute Inc., Cary, NC). According to the ratio of 1:1, patients will be assigned to the intervention group (nano-modified Runji ointment group) and placebo group. The random allocation table and random code will be kept strictly confidential, and the allocation hiding will continue throughout the experiment.

## Blinding

7

The treatment plan will blind the enrolled patients, and the investigator and clinical pharmacist will also be blinded. Only the Key Unit of Methodology in Clinical Research of Shunyi Hospital of Traditional Chinese Medicine has access to the random allocation table. Those who participated in the study and those related to the trial will also be blinded. After the study is completed, the research team can view the blind assignment. In the event of a medical emergency, it is necessary to understand the patient's previous treatment and the current treatment plan, and the researcher will unblind. The researcher will try to contact the project leader first, then contact the relevant statistician, and use a separately arranged emergency code to unblind.

## Intervention

8

All enrolled patients underwent the TCM decoction Yangxue Huoxue Decoction, a prescription for the treatment of psoriasis with blood dryness syndrome. It is composed of *Radix Angelicae sinensis, Caulis Spatholobi, Rhizoma Dioscoreae, Radix Rehmanniae recens, Rhizoma Smilacis Glabrae, Nidus Vespae,* and *Radix Clematidis*. The drug dosage form was granules, twice a day for 8 weeks, and it is provided by Guangdong Yifang Pharmaceutical Co., Ltd.

The medicine used by the intervention group is nano-modified Runji ointment. Its ingredients are Radix *A sinensis*, Fructus Cannabis, *Caulis* Spatholobi, *Caulis* Polygoni Multiflori, Fructus Aurantii, Radix *Angelicae dahuricae*, Radix *Clematidis*, and Radix Lithospermi. Preparation process: these medicines were soaked in sesame oil for 48 hours, and then fried at an oil temperature of 100°C to 120°C until they were browned, the oil was filtered, and then the medicines were nanometerized using nanotechnology to make nano ointment. The placebo ointment used by the placebo group is mainly composed of petrolatum and pigment, which makes its properties and appearance look similar to the ointment in the intervention group. The ointments for the intervention and placebo groups were obtained from the Institute of Chemistry, Chinese Academy of Sciences.

The frequency of use of the nano-modified Runji ointment and placebo ointment was twice a day for 8 weeks. The dosage of each drug was determined according to the size of the skin lesions. Approximately 2 palm areas (approximately 2% of the body surface area) can use 1 fingertip unit ointment.^[23]^ One fingertip unit refers to the amount of ointment covered from the tip of the index finger to the first interphalangeal joint with a tube with a diameter of 5 mm. The flow chart of the trial is shown in Figure 1.

**Figure 1 F1:**
[figure not shown]
The flow chart of the trial. ALT = alanine aminotransferase, AST = aspartate aminotransferase, BUN = blood urea nitrogen, Cr = serum creatinine.

## Outcomes

9

### Primary outcome

9.1

The primary outcome was the change in the psoriasis area and disease severity index score (PASI) from baseline to week 8. PASI is the gold standard for the diagnosis and evaluation of psoriasis, a simple and effective scale proposed in 1978.[^24^,^25^] The calculation method is as follows:

$$\text{PAS}{\text{I}}_{\text{H}}=({\text{E}}_{\text{H}}+{\text{I}}_{\text{H}}+{\text{D}}_{\text{H}})\times {\text{A}}_{\text{H}}\times 0.1$$

$$\text{PAS}{\text{I}}_{\text{U}}=({\text{E}}_{\text{U}}+{\text{I}}_{\text{U}}+{\text{D}}_{\text{U}})\times {\text{A}}_{\text{U}}\times 0.2$$

$$\text{PAS}{\text{I}}_{\text{L}}=({\text{E}}_{\text{L}}+{\text{I}}_{\text{L}}+{\text{D}}_{\text{L}})\times {\text{A}}_{\text{L}}\times 0.4$$

$$\text{PASI}=\text{PAS}{\text{I}}_{\text{H}}+\text{PAS}{\text{I}}_{\text{U}}+\text{PAS}{\text{I}}_{\text{T}}+\text{PAS}{\text{I}}_{\text{L}}$$

E, erythema; I, infiltration; D, scales; A, area; H, head; U, upper limbs; T, trunk; L, lower limbs. The scoring range of skin lesion area: 1, <10%; 2, 10% to 30%; 3, 30% to 50%; 4, 50% to 70%; 5, 70% to 90%; 6, 90% to 100%. The scores for I and D ranged from 0 to 4: 0, no symptom; 1, mild; 2, moderate; 3, severe; 4, very severe. E's scoring method: 0, no erythema; 1, mild erythema; 2, moderate erythema; 3, significant erythema; 4, severe erythema. The total PASI ranged from 0 to 72 points. The higher the score, the more serious the condition.

### Secondary outcome

9.2

#### Body surface area score

9.2.1

The area of skin lesions was evaluated using the palm area method.^[26]^ The fully extended area of the subject's palm represented 1% of the body surface area.

#### Visual analogue scale method

9.2.2

The visual analog scale method was used to evaluate the degree of itching of the subjects in the past week, which is represented by a 100 mm long line. 0: no itching, 100 mm: most itching, and the degree of itching is unbearable.

#### Dermatology Life Quality Index score

9.2.3

The Dermatology Life Quality Index is a questionnaire commonly used in the daily diagnosis and treatment of the Dermatology Department.^[27]^ It contains 10 questions to evaluate the impact of skin diseases on the quality of life. The score ranges from 0 to 30 points; the higher the score, the lower the quality of life.

#### TCM symptom score

9.2.4

The TCM symptom score was used to measure changes in the symptoms of blood dryness syndrome. The syndrome score scale was divided into 3 dimensions: scaly, itching, and dry mouth. The score of each dimension was 0 to 7 points, and the total score was 0 to 21 points. The higher the score, the more severe the symptoms.

All patients will be followed up by experienced investigators (≥5 years of clinical experience). The above outcome indicators will be evaluated at 0, 2, 4, 6, 8, 12, and 24 weeks. All the observed indicators are shown in Table 1.

**Table 1 T1:** Schedule for enrollment, intervention, and assessment.

Factors	Screening	Treatment period				Follow-up	
	Visit 1	Visit 2	Visit 3	Visit 4	Visit 5	Visit 6	Visit 7
	Week 0	Week 2	Week 4	Week 6	Week 8	Week 12	Week 24
Informed consent	√						
Enrollment	√						
Demographic history	√						
Medical history	√						
Physical examinations	√						
Conformation of inclusion and exclusion criteria	√						
Randomization	√						
Medication	√						
Safety index (blood routine examination, ALT/AST/BUN/Cr)	√				√		
AE		√	√	√	√	√	√
PASI/VAS/BSA score	√	√	√	√	√	√	√
TCM symptom score	√	√	√	√	√	√	√
DLQI	√				√	√	√
Take pictures of the lesions	√	√	√	√	√	√	√

#### Adverse events (AEs)

9.2.5

All adverse events (AEs) will be recorded and any serious AEs will be reported to the Research Ethics Committee within 24 hours. When AEs occur, the study investigators will request that the patient terminate the treatment and then determine whether this event was related to the nano-modified Runji ointment. The principal investigator may implement urgent safety measures to protect patients from immediate harm. If the AE is related to the nano-modified Runji ointment, it is termed as a side effect. If the side effect is mild and the patient agrees to commence, the treatment will continue after the symptoms abate or disappear. Patients will withdraw from the study if serious AEs are observed.

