### Sample size estimation

9.3

We expect that after the end of the treatment period, the PASI of patients in the intervention group will drop by 2 more than in the placebo group, with a standard deviation of 3. It is now inferred that the probability of type I error is 5% on both sides, and the probability of type II error is 20%. Therefore, 36 patients were included in the study. Considering the 10% loss to follow-up rate, each group needs to recruit 40 patients.

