### Data collection and management

9.4

Data collection and management are required before the start, during, after treatment, and during the follow-up period. Research data was recorded on the case report form form and then entered into the electronic system (double data entry). All personal private information about the patients was hidden.

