### Statistical analysis

9.5

A statistician blinded to the patient allocation for each group performed all analyses using SPSS 21.0 software (SPSS Inc, Chicago, IL). Statistical analysis will be performed on an intention-to-treat basis. The intention-to-treat analysis included all randomized patients. We will describe the data using frequency counts and proportions for qualitative variables and means ± standard deviation will be used for normally distributed quantitative variables, and median (interquartile) will be used for non-normally distributed quantitative variables. We will apply the chi-square test to examine the differences between the intervention and placebo groups for qualitative variables, the t-test to examine the differences between 2 groups for normally distributed quantitative variables, and the Wilcoxon rank-sum test for non-normally distributed quantitative variables. A generalized linear model was applied to quantitative variables with repeated measures. In this study, *P* values <.05 (two-tailed) will be considered statistical significance.

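### Section 9.2.5 takes patients with a serious adverse event out of the study, not only off the ointment, so their remaining scheduled safety and outcome assessments are lost

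*Protocol article*

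**What the plan says.** Section 9.2.5 gives different instructions by type of event.

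- Any adverse event: "When AEs occur, the study investigators will request that the patient terminate the treatment", after which relatedness to the ointment is judged.
- Mild side effect: treatment may resume once symptoms settle, if the patient agrees.
- Serious adverse event: "Patients will withdraw from the study if serious AEs are observed". No relatedness condition is attached. Reporting to the ethics committee within 24 hours is required separately.

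Other sections bear on what this withdrawal removes.

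- Section 3 describes the trial as "including an 8-week treatment period and a 16-week follow-up period", and section 8 limits ointment use to the first of these: "The frequency of use of the nano-modified Runji ointment and placebo ointment was twice a day for 8 weeks".
- Section 9.1 sets the primary outcome as PASI change from baseline to week 8.
- Table 1 schedules PASI at every visit to week 24 and adverse-event checks at weeks 2, 4, 6, 8, 12 and 24. The laboratory row, beginning "Safety index (blood routine examination, ALT/AST/BUN/Cr", is ticked at weeks 0 and 8 only.
- Section 9.4 states "Data collection and management are required before the start, during, after treatment, and during the follow-up period".
- Section 9.5 states "The intention-to-treat analysis included all randomized patients".

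**The concern.** Stopping a treatment and leaving a study are different things. Section 9.2.5 names the treatment in its rules for lesser events, then names the study in its rule for serious ones. A site that follows the text would end the patient's participation.

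The article gives safety as an objective alongside efficacy, yet the patients removed are those whose later course tells most about safety. If the event occurs in the first 8 weeks, the primary outcome value is lost too, and the reason for the loss may be connected with treatment. An analysis of all randomised patients would then need an assumption for a value that could simply have been measured. That does not contradict intention-to-treat; it makes it harder to carry out well.

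The rule also gives no protection that stopping the ointment would not give. From week 8 onward there is no study ointment to stop, so withdrawal from the study can only remove observation.

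**Working it through.** **1. Sample size, to see what the loss allowance covers.** Section 9.3 gives a difference of 2 PASI points, SD 3, two-sided 5% type I error and 20% type II error.

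n per group = 2 × (1.960 + 0.842)² × 3² / 2² = 2 × 7.85 × 2.25 ≈ 35.3, rounded up to 36. Then 36 / (1 − 0.10) = 40. Both of the protocol's figures are reproduced. (A t-distribution calculation gives 36.3, so 37; the difference is immaterial here.) The allowance is 40 − 36 = 4 losses per group from all causes.

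**2. Scheduled data lost per withdrawn patient.** The counts come from Table 1. Post-baseline assessments are: adverse-event checks and PASI at weeks 2, 4, 6, 8, 12 and 24 (6 each), DLQI at weeks 8, 12 and 24 (3), and safety laboratory tests at week 8 (1). Everything scheduled after the event is counted as lost.

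| Event between weeks | AE checks lost (of 6) | PASI lost (of 6) | Week-8 PASI | Safety laboratory test (of 1) | DLQI lost (of 3) |
|---|---|---|---|---|---|
| 0–2 | 6 | 6 | lost | lost | 3 |
| 2–4 | 5 | 5 | lost | lost | 3 |
| 4–6 | 4 | 4 | lost | lost | 3 |
| 6–8 | 3 | 3 | lost | lost | 3 |
| 8–12 | 2 | 2 | kept | kept | 2 |
| 12–24 | 1 | 1 | kept | kept | 1 |

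**3. Time already observed off treatment.** Ointment is used for 8 of 24 weeks (33%); the other 16 of 24 weeks (67%) are follow-up without it. Seeing patients off treatment is already part of the design.

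**4. How many patients.** The protocol gives no serious-event rate. Assuming 1% to 5% over 24 weeks: 0.01 × 80 = 0.8 and 0.05 × 80 = 4, so about 1 to 4 patients. If events were also spread evenly over time (a further assumption), one third would fall before week 8: 0.8 / 3 ≈ 0.3 to 4 / 3 ≈ 1.3 patients losing the week-8 PASI and laboratory test.

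**5. Power.** By normal approximation, with the section 9.3 inputs, power is 84.6% at 40 evaluable patients per group, 80.7% at 36, 78.5% at 34 and 76.0% at 32. A few withdrawals of this kind would change power little. What is lost is safety follow-up and a few outcome values whose absence may depend on treatment.

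**The case against.** The strongest reply is that the sentence is loosely worded. Read in order, the paragraph describes what happens to treatment: stop it, resume it if the event is mild, end it for good if the event is serious. On that reading nothing is lost. Section 9.2.4 says in general terms that all patients will be followed up, section 9.4 requires data after treatment, and section 9.5 analyses everyone randomised. This reading is possible and cannot be excluded. But none of those sentences addresses patients withdrawn for a serious event, and the specific rule would govern at a site. If the general and specific texts pull apart, that too calls for rewording.

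A second reply is that the article condenses a fuller approved protocol, which may provide an early-termination visit or follow-up of the event to resolution. That may be so, and the counts above cover scheduled assessments only. The point, however, concerns a rule the article states, not a detail it leaves out. An analysis plan cannot recover visits that sites were told not to hold.

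A third reply is that few patients are involved: adults up to 65 without serious primary disease, 8 weeks of treatment, and an allowance already made ("Considering the 10% loss to follow-up rate, each group needs to recruit 40 patients"). This stands for sample size and for the probable effect on the efficacy estimate. It does not stand for safety, because recruiting extra patients does not restore follow-up in those who had the event. It is also true that the serious event itself is recorded and reported, and that no patient has laboratory tests scheduled after week 8, so a late withdrawal loses visits but no scheduled laboratory data.

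**Conclusion.** The concern holds as a statement about the text as written: a serious adverse event ends the patient's scheduled observation. An event before week 8 costs the primary outcome value, the single post-baseline laboratory test and at least half of the adverse-event checks. A later event costs one or two visits. The counts rest on Table 1 and on reading withdrawal from the study literally.

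The number affected, about 1 to 4 of 80, rests on an assumed 1–5% rate. No size can be put on any efficacy bias, and none is claimed; it is probably small. The weakness is practical, not a contradiction of intention-to-treat. It should be fixed because it works against the stated safety objective and is easily avoided. Confidence is medium, since the authors may have intended only a permanent stop of treatment.

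**What to change.** Replace the sentence in section 9.2.5 with wording such as: *Patients with a serious AE permanently stop study treatment but remain in the study and attend all remaining scheduled assessments (PASI and safety laboratory tests at week 8, AEs to week 24) unless they withdraw consent.* Analyse these patients in the group to which they were randomised. If a permanent stop of treatment was the intention all along, the same sentence makes that clear.

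The cost is a short amendment to the protocol and consent form. All the visits are already in Table 1, so no visits or staff are added. Some patients may still decline to attend after a serious event, so a few values can remain missing.
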